**The THP1.1(RT) Tobacco Heating Product:**

[figure not shown]

- - - - 1. THP1.1(RT) Tobacco Heating Product Consumables

The THP1.1(RT) THP consumables (neostiks) are cylinders containing blended tobacco sheet and a filter, wrapped in a paper outer. The consumables are 83 mm in length and 5.4 mm in diameter. The tobacco section is 42 mm in length and contains 210 mg of tobacco. The total weight of a consumable is 540 mg.

The consumables are designed to only be used with the THP1.1(RT) THP device and should not be misused by either being lit in a similar way to a combustible cigarette or used in a different tobacco heating device. Once a consumable has been used, it can be discarded in a regular waste bin.

- - 1. Clinical Experience

The Sponsor has assessed a similar product in 1 completed study in Japan,^13^ and a currently ongoing study in the United Kingdom. Both studies assessed BoE and nicotine pharmacokinetics in a clinical confinement setting. The investigational product is commercially available in Japan, Italy, Canada, Romania, South Korea, Russia, and Switzerland, but is not commercially available in the UK.

- 1. Rationale for the Study

Premarketing authorisations for novel tobacco products are required by some regulators, and applications in support of such authorisations may be required to include data from clinical studies to identify any potential reduction in individuals’ risk, relative to the risk of continued smoking.

The purpose of this study is to:

- Test the hypothesis that reduction in exposure to toxicants will cause changes in health effect indicators when smokers switch to using a THP compared with smokers who continue to smoke, and that these changes are directionally similar to changes seen in smokers who cease smoking (assisted with NRT), over a period of 12 months in an ambulatory setting.
- Test the hypothesis that reductions in toxicant levels in THP emissions translate to sustained reductions in human exposure to cigarette smoke toxicants, as assessed by measuring BoE in an ambulatory setting.

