1. OBJECTIVES AND ENDPOINTS
   1. Primary Objective

- To quantitatively assess differences in primary study endpoints at 90, 180, and 360 days between subjects who continue to smoke conventional cigarettes and subjects who switch to a THP.
  1. Secondary Objectives
- To quantitatively assess differences in secondary study endpoints between subjects who continue to smoke conventional cigarettes and subjects who switch to a THP.
- To assess differences in all study endpoints between subjects who switch to a THP and subjects in the assisted smoking cessation arm.
- To assess the differences in all study endpoints between subjects who switch to a THP or undertake assisted smoking cessation, and subjects who have never smoked.
- To monitor the safety profile of subjects using THPs and combustible cigarettes, and subjects in the smoking cessation and never-smoked arms.
  1. Exploratory Objectives
- To quantitatively assess the time required to observe changes in selected primary and secondary endpoints following a switch from conventional cigarettes to a THP or assisted cessation.
- To quantitatively assess differences in the exploratory endpoints between subjects who continue to smoke conventional cigarettes, subjects who switch to a THP, subjects in the cessation arm, and subjects who have never smoked (to be reported separately).
- To investigate the profile of selected primary and secondary endpoints over the course of the study for each study arm.
  1. Endpoints
     1. Primary Endpoints

Primary endpoint biomarkers to be assessed are presented in the following table:

| **Biomarker** | **Abbreviation** | **Matrix** | **Indication** |
| --- | --- | --- | --- |
| Total 4-(methylnitrosamino)-1-(3-pyridyl)-1-butanol | Total NNAL | Urine  (24-hour) * | Metabolite of the smoke toxicant 4-(methylnitrosamino)-1-(3-pyridyl)-1-butanone (NNK) |
| 8-epi-prostaglandin F_2α_ Type III | 8-Epi-PGF_2α_ Type III | Urine  (24-hour) * | Marker of oxidative stress |
| Augmentation Index | AIx | Physiological measure | Marker of arterial stiffness and hence an indicator for cardiovascular risk |

* ambulatory collection.

- - 1. Secondary Endpoints

Secondary endpoint biomarkers to be assessed are presented in the following table:

| **Biomarker of Exposure** | **Abbreviation** | **Associated Toxicant** | **Matrix** |
| --- | --- | --- | --- |
| Carbon monoxide†† | CO | Carbon monoxide | Exhaled breath |

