The primary objective will be examined by computing levels of biomarkers at each timepoint, i.e. baseline, 90, 180, and 360 days. These data will be compared between the THP arm (Arm B) and the main control arm (Arm A) using specific contrast tests from statistical models adjusted for baseline measurements. Data will be examined and may be transformed to ensure that any assumptions associated with statistical tests or models are obeyed. Alpha level across timepoints has been adjusted using the O’Brien-Fleming approach, with 0.0471 overall available alpha at Day 360, 0.0151 at Day 180, and 0.0006 at Day 90.^28^ The significance level has been allocated at each primary endpoint based on likelihood of success to detect a significant change in biomarker levels. At Day 360, statistical comparisons between THP and control will be performed at α= 0.0451 for AIx. The remainder alpha will be distributed equally (α= 0.001) for the other 2 primary endpoints. At Day 90, only changes in BoE are expected; therefore, only Total NNAL will be statistically assessed with α=0.0006**.** For the statistical analysis performed at Day 180, an overall α level of 0.0151 will be equally distributed between the 3 primary endpoints (0.00503). If any endpoint were to be significant at Day 90 or 180, it will not be statistically assessed at Day 180 and/or 360, as appropriate, and its assigned alpha level will be equally distributed between the remaining primary endpoints.

Similarly, biomarker measures in the secondary objectives will be examined by computing levels of biomarkers at each timepoint. These data will be compared between the THP and the main control arm using specific contrast tests from statistical models adjusted for baseline measurements. Statistical comparisons for secondary endpoints will be only performed if any of the primary endpoints is significant and using the alpha level released by primary endpoints. If the statistical comparison for Total NNAL is significant at Day 90, only the secondary BoE will be analysed at Day 90 using a 0.0006 significance level. Multiplicity adjustment for family wise error of secondary endpoints will be performed using Holm’s method. If any secondary endpoint were to be significant at Day 90 or 180, it will not be statistically assessed at Day 180 and/or 360, as appropriate.

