Product use compliance is a critical part of this study, as failure to fully replace cigarettes with the THP product would reduce or cancel the expected biomarker changes that would be observed if the product is used as indicated. To aid compliance assessment we will use a haemoglobin adduct of acrylonitrile, CEVal. Acrylonitrile is below the detection limit in the THP product emissions but can be found in cigarette smoke. We will use different thresholds for CEVal in ancillary analyses to deduce product use compliance. These thresholds have been calculated based on a previous study where this biomarker was reported for a modified combustible prototype cigarette.

The interim analysis on Day 90 will be performed on a subset of subjects who were enrolled on to the study on or before the day that the 42^nd^ subject was enrolled on to Arm A, and were still enrolled on the study at Day 90. This was chosen to ensure that 30 subjects on Arm A were still enrolled on the study at Day 90 to give sufficient power to detect the statistical difference between the two arms for Total NNAL.

- 1. Safety Data Summary and Analysis

All safety data will be summarised for all safety parameters based on the safety population, stratified by study arm.

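### A primary or secondary endpoint that is significant at Day 90 or 180 gets no later Arm B versus Arm A comparison, although the primary objective asks for the difference at Days 90, 180 and 360

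*Protocol*

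**What the plan says.** Section 2.1 sets the primary objective without any condition on earlier results: "To quantitatively assess differences in primary study endpoints at 90, 180, and 360 days between subjects who continue to smoke conventional cigarettes". The rationale (Section 1.3) adds the hypothesis that lower toxicant levels in THP emissions "translate to sustained reductions in human exposure to cigarette smoke toxicants".

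Section 9.3 opens in the same spirit: "The primary objective will be examined by computing levels of biomarkers at each timepoint, i.e. baseline, 90, 180, and 360 days". It says these data will be compared between Arm B and Arm A with baseline-adjusted models. It then gives overall alpha of 0.0006 at Day 90 (Total NNAL only), 0.0151 at Day 180 (0.00503 for each primary endpoint) and 0.0471 at Day 360 (0.0451 for AIx, 0.001 for each of the other two), and adds: "If any endpoint were to be significant at Day 90 or 180, it will not be statistically assessed at Day 180 and/or 360". The alpha of such an endpoint passes in equal parts to the remaining primary endpoints. The synopsis (Statistical Methods) carries the same rule. For secondary endpoints Section 9.3 repeats it: "If any secondary endpoint were to be significant at Day 90 or 180, it will not be statistically assessed at Day 180 and/or 360".

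On the Day 90 sample, Section 9.3 says: "The interim analysis on Day 90 will be performed on a subset of subjects who were enrolled on to the study on or before". The cut-off is the date on which Arm A took in its 42nd subject, and only those remaining in the study at Day 90 count. This was chosen to ensure 30 Arm A subjects.

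**The concern.** Days 90, 180 and 360 are three durations of product use, and the objective names each. Rejecting the null at Day 90 says nothing about the difference after a year. The rule nevertheless closes the statistical question for an endpoint at its first success.

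Nothing is saved in conduct. Section 6.5 lists no stop for efficacy, subjects continue to Visit 13, and the primary endpoints are still measured at Days 180 and 360 (Appendix 15.1). Section 9.3 itself warns that failure to replace cigarettes fully would reduce or cancel the expected biomarker changes. Under the rule, a difference seen at Day 90 and later lost through return to cigarettes would remain a confirmed success, with no model-based later comparison to set against it. The endpoints that respond first are the ones whose durability would go unassessed.

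**Working it through.** **Inputs.** From Section 9.3: the alpha levels above and 30 Arm A subjects at Day 90. From Section 5.2: AIx means 25.7 and 17.5, SD 12.4, 50 completers per arm, 90% power at Day 360, alpha 0.0451. The protocol gives no effect size for Total NNAL or 8-Epi-PGF2α, so ranges are assumed for those.

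**Formula.** Two-arm F-test with n per arm: df = 2n − 2, noncentrality λ = (n/2)(Δ/SD)², power = P[F(1, df; λ) > F critical at alpha].

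**1. The plan's own figure.** Δ = 25.7 − 17.5 = 8.2; Δ/SD = 8.2/12.4 = 0.661. With n = 50 and alpha 0.0451, power is 0.898 (0.904 by the normal approximation, which gives 50 per arm for 90%). The sizing reproduces. The Day 360 split also adds up: 0.0451 + 0.001 + 0.001 = 0.0471.

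**2. Is the rule likely to apply?**

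| Test | Assumption | Power |
|---|---|---|
| Total NNAL, Day 90, alpha 0.0006, 30 per arm | effect 1.0 SD | 0.60 |
| same | 1.25 SD | 0.88 |
| same | 1.5 SD | 0.98 |
| AIx, Day 180, alpha 0.00503, 50 per arm | full 8.2-point difference already present | 0.668 |

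Arm B would have more than 30 at Day 90, so the Total NNAL powers are conservative. A Day 90 win removes both remaining Total NNAL tests (Days 180 and 360). Its only test then rests on the early-enrolled subset, with about 30 of the 65 Arm A subjects. An AIx win at Day 180 removes the Day 360 AIx test, the one for which the trial was sized.

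**3. What the redistribution is worth.** This decides whether the fix should touch it. The clause is read as passing on the alpha the winner would have had at later timepoints.

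| Recipient | Trigger | Alpha | Power, 50 per arm |
|---|---|---|---|
| AIx, Day 360 | both other primaries won earlier | 0.0451 → 0.0471 | 0.898 → 0.901 |
| AIx, Day 180 | Total NNAL won at Day 90 | 0.00503 → 0.0151/2 = 0.00755 | 0.668 → 0.717 (8.2-point difference assumed present) |
| 8-Epi-PGF2α, Day 360 | AIx won at Day 180 | 0.001 → 0.001 + 0.0451/2 ≈ 0.0236 | 0.20 → 0.58 at 0.5 SD; 0.73 → 0.95 at 0.8 SD (assumed effects) |

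The gain is 0.3 percentage points in the first row, about 5 in the second and roughly 20 to 40 in the third.

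**4. Could every endpoint simply be retested at the stated levels?** If the three timepoints are separate hypotheses, the levels sum to 0.0006 + 0.0151 + 0.0471 = 0.0628, above 0.05. The O'Brien-Fleming levels presuppose repeated looks at one hypothesis, so 5% familywise control would not be assured.

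**The case against.** Ending the test of an endpoint once its boundary is crossed is ordinary group-sequential practice. The bar is conditional and concerns formal assessment only: an endpoint not significant earlier is still tested at Day 360. Levels are computed at each timepoint, descriptive summaries by arm and timepoint continue (Section 9.1), CEVal-based compliance analyses are planned, and an exploratory objective covers the profile of selected endpoints over the study. A later estimate with interval could also appear in an SAP that is not shown.

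Much of this stands, and it rules out several stronger readings.

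- A reader might infer that the plan forbids Day 360 testing outright. It does so only for early winners.
- A reader might infer that a later relapse would be concealed. The data would be collected and summarised; what is missing is the baseline-adjusted comparison.
- A reader might join the sustained-reduction hypothesis to a 12-month horizon. In Section 1.3 the words "over a period of 12 months in an ambulatory setting" belong to the separate hypothesis on health effect indicators. The exposure hypothesis gives no duration, though Day 90 alone is thin support for it.
- A reader might conclude that the redistribution is worthless and should go. That holds only for AIx at Day 360.

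The group-sequential defence does not remove the point. It fits looks at one hypothesis on accumulating data, whereas the objective here names each duration. Nor can the matter be left to the SAP as a missing detail: the protocol positively states that the endpoint will not be statistically assessed.

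**Conclusion.** The concern holds in this form: Section 9.3 and the synopsis exclude later statistical assessment of any early winner, in conflict with an objective that asks for the B-A difference at Days 90, 180 and 360 and with the sustained-reduction hypothesis. Most exposed is Total NNAL, which after a Day 90 win loses 2 of its 2 later tests. How likely that is depends on an assumed effect: power 0.60 to 0.98 for 1.0 to 1.5 SD with 30 per arm. AIx would lose its Day 360 test with probability about 0.67 if the full planned difference were present at Day 180 with 50 per arm.

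The documents do not support going further and deleting the redistribution, or retesting everything at the stated levels. The first can cost another primary endpoint far more than 0.3 points of power; the second leaves familywise control unproven. The defect lies in the ban on later assessment, not in the alpha scheme as such.

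**What to change.** In Section 9.3 and the synopsis, replace the statement that an early-significant endpoint will not be statistically assessed with three statements:

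- the endpoint needs no further test to retain its early rejection;
- the baseline-adjusted B-A contrast with confidence interval will be estimated and reported at Days 90, 180 and 360 for every primary endpoint, and likewise for secondary endpoints, whatever the earlier result;
- any claim of a sustained effect rests on the Day 360 contrast.

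The redistribution of alpha may stay. State that the later contrasts for early winners are supportive and outside the alpha-controlled family, unless the sponsor reserves alpha for them and confirms familywise control.

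Cost: wording and slightly more analysis, with no new visits, samples or subjects and no loss of power for the other endpoints. The downside is that later contrasts for early winners are not alpha-controlled, so a sustained-effect claim for them is supportive unless alpha is reserved.

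### Section 9.3 hands the alpha of an early-rejected primary to two recipients in full, so joint primary-plus-secondary error can reach about 10% if AIx is rejected at Day 180

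*Protocol*

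**What the plan says.** Section 9.3 of the Protocol sets an alpha for each look, "with 0.0471 overall available alpha at Day 360, 0.0151 at Day 180, and 0.0006 at Day 90", and divides it among three primaries.

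- Day 90: "only Total NNAL will be statistically assessed with α=0.0006".
- Day 180: 0.0151 is shared equally, 0.00503 to each primary.
- Day 360: "At Day 360, statistical comparisons between THP and control will be performed at α= 0.0451 for AIx", and "The remainder alpha will be distributed equally (α= 0.001) for the other 2 primary endpoints".

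Two rules then say what happens to the alpha of a rejected primary.

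- Rule 1 applies to a rejection at Day 90 or 180. The endpoint is not tested again and "its assigned alpha level will be equally distributed between the remaining primary endpoints". The synopsis (Statistical Methods) repeats this rule.
- Rule 2 opens the secondary endpoints once any one primary is significant, "using the alpha level released by primary endpoints", with Holm's adjustment among the secondaries. The one worked example is a Total NNAL rejection at Day 90, after which "only the secondary BoE will be analysed at Day 90 using a 0.0006 significance level".

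**The concern.** A rejected hypothesis can pass on its alpha once. Rule 1 gives all of it to the remaining primaries. Rule 2 gives the alpha released by primaries to a second family, and its example shows a full release, because 0.0006 is the whole Day 90 level. Nothing divides the alpha between the two recipients, and nothing makes the secondaries wait until every primary has been rejected. Holm's method protects against errors within the secondary family only, so it cannot recover alpha already used on primaries.

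The protocol fixes these levels to four or five decimals, so this is a fault in what is stated and not a detail left to the SAP. At stake is the error rate of the full set of confirmatory claims after an early primary success. The study is also open-label with two interim analyses, so an unsettled rule could be interpreted after results are known.

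**Working it through.** **The plan's own figures.** Day 360: 0.0451 + 0.001 + 0.001 = 0.0471. Day 180: 0.0151 / 3 = 0.00503. Both agree with Section 9.3. For AIx, the sample size section gives means of 25.7 and 17.5 (difference 8.2), SD 12.4, two-sided alpha 0.0451 and 90% power. The standard two-means formula then gives 50 per arm, as stated.

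**Nominal alpha under both rules read literally**

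- AIx rejected at Day 180. At Day 360 Total NNAL and 8-Epi-PGF2α each have 0.001 + 0.0451/2 = 0.02355, together 0.0471. The secondaries also receive 0.0451. Total: 0.0471 + 0.0451 = 0.0922, against 0.0471 available. If the families are independent, 1 − (1 − 0.0471)(1 − 0.0451) = 0.0901.
- Total NNAL rejected at Day 90 and AIx at Day 180. At Day 360 8-Epi-PGF2α has 0.001 + 0.001 + 0.0451 = 0.0471 and the secondaries have 0.001 + 0.0451 = 0.0461. Total: 0.0932.
- Only Total NNAL rejected early. At Day 360 AIx has 0.0451 + 0.0005 = 0.0456, 8-Epi-PGF2α has 0.0015 and the secondaries have 0.001. Total: 0.0481, an excess of 0.001.

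**Joint family-wise error over all three looks.** The Section 9.3 rules were simulated with independent endpoints. Truly affected primaries are rejected at their first look and everything else is null. The protocol gives no between-visit correlation, so the range runs from the pattern for equally spaced looks to a constant 0.5.

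| Primaries truly affected and rejected early | Joint error, literal reading |
|---|---|
| AIx | 9.4% to 10.1% |
| AIx and Total NNAL | 9.6% to 10.3% |
| Total NNAL only | 6.1% to 6.6% |

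With no correlation between visits, an extreme for repeated measures on the same subjects, the first two rows reach 10.3% and 10.7%. With all three primaries affected there is no double use, and the error is 5.4% for equally spaced looks.

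**Baseline.** The levels 0.0006, 0.0151 and 0.0471 applied to a single hypothesis give 5.2% for equally spaced looks. The listed boundaries as a whole give 5.2% to 5.8%, so not all of the excess over 5% comes from double use. For early Total NNAL only, removing the double use lowers 6.1% to about 5.6%, and 6.6% to about 6.0%.

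**Each family alone.** With Total NNAL and AIx rejected early, the chance of a false claim is 4.9% to 5.2% for 8-Epi-PGF2α and 4.9% to 5.4% for the secondary family.

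**Can the worst case occur?** With 50 per arm and the full Day 360 effect already present at Day 180, AIx has about 67% to 69% power at 0.00503.

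**The case against.** A near-nominal reading fits the text. The level a primary used at the look where it was rejected goes to the secondaries at that look, and its later-look levels go to the remaining primaries. The Day 90 example matches this, and an SAP, which Section 9.1 promises, could spell it out. This shows the conflict is easy to repair, but Section 9.3 does not state that reading, and its two general rules attach no look to the alpha they release.

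The large figure also belongs to a narrow case. AIx holds 0.0451 of the 0.0471, so AIx must be rejected at Day 180 while another primary and the whole secondary family are null. The introduction reports broad reductions in exposure markers after switching, so a wholly null secondary family is unlikely if the product works. A rejection first made at Day 360 causes no double use, because Rule 1 covers only Days 90 and 180. Positive correlation among endpoints would lower the figures. All of this stands, and it makes the 10% conditional.

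A reader might go further and infer that neither the primary nor the secondary claims have a controlled error rate, or that the long list of secondary biomarkers makes matters worse. The documents do not support either inference. Redistribution among the primaries keeps their Day 360 total at 0.0471, each family alone stays near 5%, and Holm's method handles the number of secondaries. Only the combined set of claims exceeds its budget.

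**Conclusion.** The concern holds as a conflict between two stated rules, with a conditional consequence. Read literally, they allow 0.0922 of nominal alpha at Day 360 against 0.0471 available once AIx has been rejected at Day 180. Joint error over primaries and secondaries is then about 9.4% to 10.3%, compared with 5.2% to 5.8% from the listed boundaries alone. An early rejection of Total NNAL only adds about half a point.

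These figures assume independent endpoints, a null secondary family, at least one null primary and the between-visit correlations described. The textual conflict depends on none of these assumptions. The small excess over 5% in the boundaries themselves is a separate matter that settling the recipient does not remove.

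**What to change.** Give each piece of released alpha one recipient, and write the same rule in Section 9.3 and in the synopsis. Keep the rule that a significant endpoint is not tested again. It shares a sentence with the redistribution rule and would be lost if that sentence were deleted whole.

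A rule that keeps both recipients:

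- The level a primary used at the look where it is rejected goes to the secondaries at that look, as in the Day 90 example at 0.0006.
- Its levels for later looks go to the remaining primaries. They pass to the secondaries only when every primary has been rejected and none is left to test.

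This gives about 5.6% to 6.0% in the worst case. The cost is that, after an early AIx rejection, the secondaries no longer also receive the Day 360 alpha while another primary is still to be tested.

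The alternative is to drop redistribution to the primaries and send released alpha only to the secondaries. It gives about 5.5% to 5.9%. The price falls on a primary endpoint: after early rejection of Total NNAL and AIx, 8-Epi-PGF2α would be tested at 0.001 on Day 360 instead of 0.0471. For a standardised effect the size of that assumed for AIx (8.2/12.4 = 0.66) and 50 per arm, power would be about 47% instead of 90%. If this option is chosen, that cost should be stated.

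Either change is a few sentences in two places and needs no new data. It should be settled before the Day 90 interim results are known.

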| Serum lipids (high-density lipoprotein [HDL], low-density lipoprotein [LDL], total cholesterol, triglycerides) | | HDL/LDL/ CholTotal/Trigly | Metabolic status | Serum |
| **Other Measures** | | | | |
| Creatinine (urine; 24-hour) † | | | | |
| **Physiological Measures** | | | | |
| Body weight/waist circumference | | | | |
| Carotid/femoral pulse wave velocity | | | | |
| 6-minute walking test | | | | |
| Finger plethysmography | | | | |
| **Questionnaires** | | | | |
| Fagerström Test for Cigarette Dependence (FTCD) † | | | | |
| Product Satisfaction † | | | | |
| Smoking Cessation Quality of Life | | | | |
| Self-reported product use (eDiary/paper diary) † | | | | |
| Cough and Shortness of Breath VAS | | | | |
| **Safety** | | | | |
| Physical examination † | | | | |
| Vital signs † | | | | |
| Electrocardiogram (ECG) † | | | | |
| Clinical laboratory evaluations † | | | | |
| Lung function test (spirometry) | Peak flow | | | |
|  | Forced vital capacity (FVC) | | | |
|  | Forced expiratory flow (FEF) 25-75% | | | |
|  | Forced expiratory volume in 1 second (FEV_1_) | | | |
| Adverse events (AE)/SAE recording † | | | | |

* Ambulatory collection.

† Blood pressure will be assessed using the statistical analysis as described in Section 9.3. Other endpoints may be analysed using a statistical method that will be described in the Statistical Analysis Plan.

†† The assessments on Days 120 and 150 will be used in the Day 90 interim analysis, the assessments on Days 210 and 240 will be used in the Day 180 interim analysis, and the assessments on Days 300 and 330 will be used in the final analysis on Day 360.

- - 1. Exploratory Endpoints

Body fat will be measured and reported.

Sample collections for the following exploratory analyses will also be taken and will be reported separately:

- Dihydrobiopterin/tetrahydrobiopterin (BH2/BH4) ratio in plasma
- Transcriptomics (nasal epithelial cells)
- Transcriptomics (WBC)
- Serum nuclear magnetic resonance (NMR) lipoprotein
- Serum metabolomics

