Abbreviations: 1-OHP = 1-hydroxypyrene; 2-AN = 2-aminonaphthalene; 3-HPMA = 3-hydroxypropylmercapturic acid; 3-NTyr = 3-nitrotyrosine; 4-ABP = 4-aminobiphenyl; 4-HNE = 4-hydroxy-nonenal + metabolites; 8-Epi-PGF_2α_ = 8-Epi-Prostaglandin F_2α_ Type III; 11-dTx B2 = 11-dehydrothromboxane B2; AE = adverse event; AIx = Augmentation Index; BH2/BH4 = dihydrobiopterin/tetrahydrobiopterin ratio; BMI = body mass index; CEMA = 2-cyanoethylmercapturic acid; CEVal (Hb adduct) = N-(2-cyanoethyl)valine (haemoglobin adduct); CholTotal = total cholesterol; CO = carbon monoxide; ECG = electrocardiogram; ET-1 = endothelin-1; Fib = fibrinogen; FSH = follicle-stimulating hormone; FTCD = Fagerström test for cigarette dependence; Gluc = glucose; HDL = high-density lipoprotein; HEMA = 2-hydroxyethylmercapturic acid; HMCys = homocysteine; HMPMA = 3-hydroxy-1-methylpropylmercapturic acid; hsCRP = high-sensitivity C-reactive protein; LDL = low-density lipoprotein; MCP-1 = monocyte chemotactic protein 1; MHBMA = monohydroxybutenyl-mercapturic acid; NMR = nuclear magnetic resonance; NNAL = 4-(methylnitrosamino)-1-(3-pyridyl)-1-butanol; NNN = N-nitrosonornicotine; NO = nitric oxide; o-Tol = ortho-toluidine; PAI-1 = plasminogen activator inhibitor-1; SAE = serious adverse event; SELE – E-selectin; s-ICAM1 = soluble intercellular adhesion molecule-1; S-PMA = S-phenylmercapturic acid; TNeq = total nicotine equivalents (nicotine, cotinine, 3-hydroxycotinine and their glucuronide conjugates); tPA = tissue plasminogen activator; WBC = white blood cell.

^a^ Arms A and B only.

^b^ Arm B only.

^c^ Female subjects of childbearing potential. Performed in serum at Screening and in urine at all other times.

^d^ Symptom driven physical examination.

^e^ Includes serum biochemistry, haematology, and urinalysis.

^f^ Spirometry conducted pre and post-bronchodilator.

^g^ Subjects will not be allowed to use a study product within the 30 minutes prior to CO assessments.

^h^ To begin the day before each study visit.

^i^ Blood pressure and lung function tests (spirometry) as physiological endpoints are presented with safety parameters.

^j^ Arms A, B, and D only.

^k^ Arms B and D only.

^l^ Subjects may be rescreened to confirm CO levels if they have a low CO level at screening

^m^ Visit should occur between 1630 and 2100 hours

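### Blood pressure, a safety measure, and apparently spirometry have their only formal Arm B versus Arm A comparison inside the conditional, Holm-adjusted secondary procedure, which lowers its sensitivity to a worsening.

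*Protocol*

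**What the plan says.** The Secondary Endpoints table in Section 2 of the protocol has a safety block that includes vital signs and spirometry. Vital signs carry a dagger, and the dagger note says "Blood pressure will be assessed using the statistical analysis as described in Section 9.3". The note leaves the other daggered rows to a method in the statistical analysis plan. Spirometry has no dagger. Footnote i of the Schedule of Assessments (Appendix 15.1) puts the two together: "Blood pressure and lung function tests (spirometry) as physiological endpoints are presented with safety parameters".

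Section 9.3 then governs the comparison of Arm B (tobacco heating product) with Arm A (continued smoking):

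- **Precondition:** "Statistical comparisons for secondary endpoints will be only performed if any of the primary endpoints is significant". The alpha used is whatever those primaries release.
- **Multiplicity:** "Multiplicity adjustment for family wise error of secondary endpoints will be performed using" Holm's method.
- **Day 90:** if Total NNAL is significant, "only the secondary BoE will be analysed at Day 90 using a 0.0006 significance level".
- **Later visits:** a secondary endpoint that is significant at one visit is not tested again at the next.

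The safety objective in Section 2 is "To monitor the safety profile of subjects using THPs and combustible cigarettes" and in the cessation and never-smoked arms. Section 9.4 provides a summary of all safety parameters by arm in the safety population. It states no between-arm contrast or interval. Nothing in the protocol exempts blood pressure or spirometry from the Section 9.3 conditions.

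**The concern.** Preconditions and familywise control exist to limit false claims of benefit. When the same measure also serves as a safety measure, they work the other way and make a real worsening harder to detect. Under the protocol, whether and how sharply blood pressure is formally compared with continued smoking depends on Total NNAL, 8-Epi-PGF2α and Augmentation Index (AIx), none of which is a safety measure. Nearly all of the Day 360 alpha (0.0451 of 0.0471) sits on AIx, so most of the available sensitivity to harm depends on AIx being significant. At Day 90 no formal blood pressure or spirometry comparison is possible under any result.

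At stake is the value of the only inferential result that the protocol states for these measures. A difference that is untested, or tested at a very small threshold and found non-significant, says little about absence of harm.

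**Working it through.** **1. The plan's own figures reproduce.** Section 5.2 gives AIx means of 25.7 and 17.5, SD 12.4, alpha 0.0451 and 90% power. The standardised effect is d = 8.2/12.4 = 0.66. Then n = 2(2.004 + 1.282)²/0.6613² = 49.4, or 50 per arm, which matches the target. Exact noncentral-t power at 50 per arm is 89.8%. The alpha splits also reproduce: 0.0151/3 = 0.00503 at Day 180, and (0.0471 − 0.0451)/2 = 0.001 for each of the two other primaries at Day 360.

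**2. Size of the secondary family (assumption).** Counting rows of the endpoint table that allow a B versus A comparison: 13 biomarkers of exposure + 19 biomarkers of biological effect (four lipids counted separately) + 5 physiological + 2 cough and breathlessness scales + 4 spirometry + 2 blood pressure = 45. A plausible range is 35 to 45.

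**3. Holm threshold.** Suppose the 13 biomarkers of exposure are rejected first. The next smallest p-value is compared with α/(45 − 13) = α/32.

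**4. Power of one measure.** The noncentrality is d/√(1/n₁ + 1/n₂), two-sided. With baseline correlation ρ, d is replaced by d/√(1 − ρ²). For a 0.5-SD worsening at 50 v 50, the noncentrality is 0.5/0.2 = 2.5. With ρ = 0.6 it is (0.5/0.8)/0.2 = 3.125. Neither the 0.5 SD nor the 0.6 comes from the protocol, which gives no SD or relevant change for blood pressure or spirometry.

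| Alpha available | Threshold | Power, ρ = 0 | Power, ρ = 0.6 |
|---|---|---|---|
| Unconditional 0.05 | 0.05 | 70% | 87% |
| 0.0451 (AIx, Day 360) | 0.00141 | 22% | 44% |
| 0.00503 (one primary, Day 180) | 0.000157 | 8.5% | 22% |
| 0.001 (one other primary, Day 360) | 0.000031 | 4% | 12% |

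These figures are conditional on that alpha having been released. If it is not released, no test is made.

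**5. Sensitivity.**

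- *Full Holm simulation.* With 45 independent endpoints and ρ = 0, it gave 9.6% at 0.00503 and 4.4% at 0.001, close to the fixed-threshold figures.
- *Smaller family.* With 35 measures the divisor is 35 − 13 = 22, and the ρ = 0 column becomes 26%, 10% and 4.6%.
- *Larger effect.* At 0.66 SD, ρ = 0.6 and 0.0451 released, power is about 80% at 50 v 50 and 96% at 50 v 150. With ρ = 0 at 50 v 150 it is 79%.

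**6. How much alpha is released.** Section 9.3 gives secondaries the alpha released by significant primaries. It also gives the alpha of a primary that is significant early to the remaining primaries. What is left for secondaries after an early Total NNAL result is therefore unclear, which is why three amounts are shown.

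**The case against.** The strongest reply is that the safety objective is to monitor, not to test, and that monitoring is unconditional. Section 9.4 summarises all safety data by arm whatever the primaries show. Section 9.1 gives n, mean and SD by timepoint, from which an unadjusted difference and interval can be computed. Interim reports cover Days 90 and 180, and clinically relevant worsening is recorded as an adverse event. That stands. A reader might infer that the plan forbids any comparison of blood pressure or spirometry when the primaries fail. It does not: it withholds the statistical comparison, while results by arm are always shown. Failure of every primary is also unlikely, because a Total NNAL difference is expected.

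It is also fair to say that spirometry's place in Section 9.3 is not stated. It rests on the missing dagger and footnote i, whereas spirometry is listed under safety and Section 9.4 covers all safety parameters. Only blood pressure is sent to Section 9.3 explicitly.

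A further reply is that footnote i treats both as physiological endpoints, for which multiplicity control is proper. That is right for a claim of improvement but does not answer the safety reading. Nor can the point be left wholly to the statistical analysis plan, since the protocol itself fixes the method for blood pressure. The plan nowhere says that non-significance will be read as absence of harm; the risk is that nothing rules it out.

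**Conclusion.** The point holds for blood pressure as stated in the protocol, and for spirometry by inference. The only formal B versus A comparison that the protocol states for these measures is conditional on a primary result, uses released alpha under Holm, and is absent at Day 90. At each released amount its threshold is well below that of an unconditional 0.05 test. For a 0.5-SD worsening at the targeted 50 v 50, power drops from 70% to between 4% and 22%, or from 87% to between 12% and 44% with baseline correlation 0.6. Effect size, correlation, family size and order of rejection are assumptions.

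A reader might infer that a real worsening would usually be missed. The documents do not support that as a general statement. It depends on the size of the worsening, the baseline correlation, the number of Arm B completers and which primary releases alpha. At 0.66 SD, with correlation 0.6 and AIx significant, the test keeps about 80% power or more. The supported conclusion is a reduced sensitivity to harm that serves no purpose for a safety measure and is cheap to remove.

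**What to change.** In Section 9.3 and the dagger note to the Secondary Endpoints table:

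- State that, for the safety reading, blood pressure is outside the primary precondition, the released alpha and Holm. Say explicitly whether spirometry is routed the same way, and if so give it the same treatment.
- Report the baseline-adjusted B − A difference with an unadjusted 95% confidence interval at Days 90, 180 and 360, whatever the primary results and whatever was significant at a previous visit.
- State that a non-significant result is not read as absence of harm; the reading rests on the interval.
- Keep any claim that these measures improve inside the conditional Holm family.

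The cost is wording and a few table columns, with no new data or subjects. The downside is that the safety intervals are not adjusted for multiplicity, so some chance differences will need explaining, and the intervals cannot support claims of benefit. They will also be fairly wide: at 50 v 50 without baseline adjustment the half-width is 1.98 × 0.2 = 0.40 SD.
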